**Objective:**

The aim of this study will be to examine whether a multicomponent quality-improvement strategy that uses protocoled TLTs as the default ICU care-planning approach for critically ill patients with advanced medical illnesses will decrease duration and intensity of nonbeneficial ICU care without changing hospital mortality.

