**Figure 1 figure1:**
[figure not shown]
Implementation strategy for time-limited trials. ICU: intensive care unit.

We hypothesize that a multicomponent quality-improvement intervention, informed by stakeholder input and that uses protocoled TLTs as the default ICU care-planning approach for critically ill patients with advanced medical illnesses, will decrease the duration and intensity of nonbeneficial ICU care without changing hospital mortality. We will examine our hypothesis with the specific aims discussed in the following sections.

#### Aim 1

Aim 1 consists of identifying barriers and facilitators to performing TLTs in ICU patients with advanced medical illnesses using focus groups of physicians and semistructured interviews of patients and their families.

#### Aim 2

Aim 2 consists of examining whether a multicomponent quality-improvement intervention using TLTs as the default care-planning approach for ICU patients with advanced medical illnesses reduces duration and intensity of nonbeneficial ICU treatments

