###### Time-Limited Trial Protocol

Physician-led family meetings will be conducted using a standardized protocol, which includes: (1) introductions, (2) summary of ICU course, (3) discussion of short- and long-term prognosis, (4) risks and benefits of aggressive ICU care, and (5) eliciting patients’ preferences for care during critical illness and/or at the end of life (see Multimedia Appendix 2 and Figure 1). Based on discussion of these elements, if patients and surrogate decision makers wish for a palliative approach, the patient will be transitioned to comfort-focused care. If patients and surrogate decision makers prefer aggressive ICU care, a TLT will be performed. For the TLT, care providers and surrogate decision makers will identify specific clinical parameters that will be used to determine whether patients are improving or worsening. Care providers will recommend a time period for which these parameters will be followed and likely actions to be taken at the end of the trial based on improvement or worsening. In the follow-up meeting, care providers will review trends in clinical parameters; they will also redefine prognoses based on these trends and additional clinical information obtained since the last meeting. Based on this information, recommendations regarding the next steps for care will be made. If the patients and surrogate decision makers opt for a palliative approach, comfort-focused care will be provided. If they prefer continuation of aggressive care, another TLT will be negotiated. This iterative process will be continued, with sequential meetings performed at the discretion of the ICU team (see Figure 1).

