###### Outcomes and Measurements

All outcomes will be collected in both the pre- and postintervention periods. The primary outcome will be ICU length of stay. Secondary outcomes will include hospital length of stay, days receiving life-sustaining treatments (eg, mechanical ventilation, use of vasopressor medications, and renal replacement therapy), number of attempts at cardiopulmonary resuscitation (CPR), number of invasive procedures (eg, central venous or arterial catheterization, thoracentesis, paracentesis, lumbar puncture, and endoscopy), and outcomes of hospitalization (eg, death, discharge to hospice, skilled nursing facility, or home). These data will be collected from retrospective chart review by trained case managers using standardized data abstraction forms.

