###### Analysis Plan

Primary and secondary outcomes will be compared before and after the intervention [46-48]. Days in ICU, days in hospital, and days receiving life-sustaining treatments will be compared using Wilcoxon rank-sum tests [49,50]. ICU and hospital mortality rates will be compared using χ^2^ tests. Other continuous and categorical outcomes will be compared between groups using *t* tests or χ^2^ tests, respectively, or equivalent nonparametric approaches for variables that are nonnormally distributed. Multivariable regression models will be used to examine the effects of covariates, such as patient demographics, comorbid conditions, severity of illness, and hospitals, on study outcomes [49,50]. Primary and secondary outcomes before and after the intervention will also be analyzed and will be stratified by ICU survivors and nonsurvivors. Days receiving ICU care, days receiving life-sustaining treatments, number of invasive procedures, and number of CPR attempts among patients who did not survive hospitalization will be considered nonbeneficial treatment and will be compared before and after the intervention.

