###### Expected Results

We expect to find fewer ICU days, hospital days, and days of life-sustaining treatments after the TLT intervention. We also expect a fewer number of attempts at CPR and other invasive procedures. We expect mortality rates to remain unchanged before and after the intervention. We expect reductions in ICU days, days receiving life-sustaining treatments, and number of invasive procedures after the intervention to be greater among patients who died during hospitalization than among survivors.

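### Hospital mortality alone cannot carry the unchanged-mortality claim, because the intervention can change where deaths occur; add death-or-hospice beside it

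*Protocol article*

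**What the plan says.** The abstract's Objective is that the strategy "will decrease duration and intensity of nonbeneficial ICU care without changing hospital mortality". The Objectives section of the Introduction repeats this as the hypothesis, and Expected Results adds: "We expect mortality rates to remain unchanged before and after the intervention".

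The test is in the Analysis Plan: "ICU and hospital mortality rates will be compared using" χ² tests. No other mortality measure is named.

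Outcomes and Measurements lists, as a secondary outcome, "outcomes of hospitalization (eg, death, discharge to hospice, skilled nursing facility, or home". Death and hospice discharge are therefore separate categories. On the data source it says: "These data will be collected from retrospective chart review by trained case managers using standardized data abstraction forms". No vital status after discharge, or at a fixed day from ICU admission, is stated.

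On what the intervention does, the Time-Limited Trial Protocol section says that if patients and surrogates want a palliative approach, "the patient will be transitioned to comfort-focused care". Expected Results says: "We expect to find fewer ICU days, hospital days, and days of life-sustaining treatments after the TLT intervention".

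**The concern.** In-hospital death is the product of two things: whether the patient dies, and whether that happens before discharge. The intervention is meant to influence care choices near the end of life and to shorten stays, so it may act on the second as well as the first. ICU mortality has the same problem one step earlier, since a patient who leaves the ICU for comfort care and dies on the ward is not an ICU death.

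This is a matter of how the outcome is defined. A larger sample or a different test would not separate survival from place of death.

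At stake is the second half of the hypothesis. A flat hospital mortality could hide extra deaths offset by a move to hospice, and a lower one could reflect that move alone. A higher one could arise if more patients received comfort care in hospital and died there rather than after discharge.

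**Working it through.** **The plan's own figure.** 960 screened × 0.15 eligible × (1 − 0.10) = 129.6, so 130 per period, as stated. The detectable difference in ICU stay is (1.960 + 0.842) × 3.7 × √(2/130) = 1.29 days, against the stated 1.3. Both reproduce. They concern ICU stay only; the article gives no mortality rate, margin or power.

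**Inputs for the illustration.** n = 130 per period is from the article. A baseline of 50% in-hospital death (65) and 10% hospice discharge (13) is assumed. The nearest figure in the article is 86% who died or left in a severely compromised state, which does not give deaths separately.

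**Formula.** For counts a and b out of 130, with pooled proportion p = (a + b)/260, z = (b − a)/130 ÷ √(2p(1 − p)/130). This is the uncorrected χ² test.

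**Scenario A: 13 deaths move to hospice, nothing else changes.**
- Hospital deaths: 65 to 52, or 50% to 40%. p = 0.45, standard error 0.0617, z = −1.62, p-value about 0.11.
- Death or hospice: 65 + 13 = 78 before, 52 + 26 = 78 after. No change, as is right when no life is saved.

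**Scenario B: 13 deaths move to hospice and 13 would-be survivors die in hospital.**
- Hospital deaths: 65 − 13 + 13 = 65. 50% in both periods, p-value 1.0.
- Death or hospice: 78 before, 65 + 26 = 91 after, or 60% to 70%. p = 0.65, standard error 0.0592, z = 1.69, p-value about 0.09. The 95% interval for the difference is 0.10 ± 1.96 × √(0.6 × 0.4/130 + 0.7 × 0.3/130) = 0.10 ± 0.115, or −1.5 to 21.5 points.
- Hospice alone: 13 to 26. p = 0.15, standard error 0.0443, z = 2.26, p-value about 0.02.

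**Range over the assumptions.** Suppose true deaths are unchanged and a share of all patients die in hospice instead of in hospital. The probability that the hospital mortality test is significant at two-sided 0.05 is:

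| Assumed baseline hospital mortality | 5% relocated | 10% relocated | 15% relocated |
|---|---|---|---|
| 30% | 0.15 | 0.46 | 0.83 |
| 40% | 0.13 | 0.39 | 0.74 |
| 50% | 0.12 | 0.37 | 0.69 |
| 60% | 0.13 | 0.37 | 0.68 |

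At any of these baselines, a true rise of 10 points with 10% relocated leaves observed hospital mortality exactly flat.

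**The case against.** The strongest reply is that the plan already looks at hospice. Disposition is a secondary outcome collected in both periods, and the Analysis Plan compares secondary outcomes before and after, with χ² tests for categorical ones. In Scenario B, hospice going from 13 to 26 would show there (p about 0.02 taken alone). This stands. The information is not missing; what is missing is any link between it and the mortality statement.

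Second, the claim is worded as hospital mortality, and that is what is measured. This holds for the Objective and the hypothesis, but Expected Results speaks of mortality rates without that qualifier.

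Third, the composite is no clean substitute. A patient who would have gone to a nursing facility but prefers hospice raises it without harm. At 130 per period it is also imprecise: 78 against 91 is not significant, so it too could be read as unchanged on a p-value alone. Both points stand. They are reasons to put the composite beside hospital mortality and to report an interval.

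A reader might also infer that the bias favours the intervention. The article does not support that. It does not say where comfort-focused care is given, and comfort care in hospital may raise in-hospital death. Nor do fewer hospital days necessarily shorten the observation of death, since a stay that ends sooner in death is fully observed.

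**Conclusion.** The point holds as a limit on what the mortality statement can show. The article tests that statement only with ICU and in-hospital death, while describing an intervention that can change the place of death. A relocation of 10% of patients' deaths shifts hospital mortality by 10 points or hides a true rise of that size. The size rests on assumed baselines and an assumed relocation; that relocation will happen is possible but not established.

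Three stronger readings are tempting and not supported. The plan does not state that hospice discharge counts as survival; that follows only from using hospital mortality with hospice listed apart. It does not present mortality as a safety check; it is part of the hypothesis. And a hospice shift alone would not reliably be declared a mortality reduction: 65 against 52 gives p about 0.11, and the chance of significance for a 10-point shift is 0.37 to 0.46.

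The primary outcome, ICU length of stay, is not affected. This should be fixed, but it is not critical to the study.

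**What to change.** In Outcomes and Measurements and in the Analysis Plan:

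- Keep hospital mortality as it is.
- Add a prespecified composite of in-hospital death or discharge to hospice. Compare it before and after with a confidence interval, and show its two components beneath it.
- State that mortality was unchanged only if both hospital mortality and the composite support it, judged from the intervals and not from a p-value above 0.05. Otherwise limit the conclusion to in-hospital death.
- Label ICU mortality as affected by place of death.

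The cost is analysis wording only, because disposition including hospice is already abstracted in both periods. The downside is that the composite includes patients who choose hospice by preference or who live for some time after discharge. That is why it stands beside hospital mortality and does not replace it.

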###### Setting and Study Design

The study will be conducted in medical ICUs of three LAC DHS hospitals using a before-and-after study design. The study will be conducted sequentially among the three hospitals to allow investigators to modify and improve the implementation strategy over the course of the study based on clinician feedback (see Multimedia Appendix 1). For each hospital, we will collect preintervention data during the first 4 months and examine outcomes for a 4-month period after implementing the study intervention (see Multimedia Appendix 1). There are 52 medical ICU beds among the three hospitals. We anticipate that 960 patients will be admitted and screened in both the pre- and postintervention periods across the three medical ICUs. Based on our preliminary data, we estimate that 15% will be priority 3 and 4 patients who are candidates for intervention and 10% will be excluded due to lack of surrogate decision makers. As such, we estimate studying 130 patients during each 4-month period. Using alpha=.05 (two-sided), beta=.20 (80% power), and mean ICU stay of 6.5 days (SD 3.7) from our previous study [16], we expect to be able to detect a difference of 1.3 ICU days between time periods.

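### The claim of unchanged hospital mortality is matched only to a chi-square test of difference, and about 130 patients per period are too few for a non-significant result to support it

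*Protocol article*

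**What the plan says.** The hypothesis under Objectives is that the intervention "will decrease the duration and intensity of nonbeneficial ICU care without changing hospital mortality". The Abstract's objective carries the same two-part claim. Expected Results repeats it: "We expect mortality rates to remain unchanged before and after the intervention".

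The Analysis Plan states that "ICU and hospital mortality rates will be compared using" chi-square tests. It also plans regression on the trial's outcomes: "Multivariable regression models will be used to examine the effects of covariates, such as patient demographics, comorbid conditions, severity of illness, and hospitals, on study" […]. The section Outcomes and Measurements lists death within a secondary outcome, "outcomes of hospitalization (eg, death, discharge to hospice, skilled nursing facility, or home").

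Under Setting and Study Design, "we estimate studying 130 patients during each 4-month period". That number is supported by a detectable difference in ICU days. No corresponding statement is made for mortality.

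**The concern.** The hypothesis asserts no change, while the named test can only detect a change. If the test is not significant, the plan offers no other stated route to the conclusion it expects. The study could then report a shorter ICU stay with mortality unchanged while its data are compatible with a rise in deaths of 10 points or more.

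This matters more here than for an ordinary secondary outcome, because mortality is the condition under which a shorter stay counts as a benefit. The rank-sum test on ICU days gives the same rank to a stay ended by death and an equal stay ended by live discharge.

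Hospital mortality can also be moved by the intervention itself. Some patients will be transitioned to comfort-focused care, and a patient discharged to hospice is not counted as a hospital death. The hospital death rate could stay flat because deaths have shifted elsewhere.

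**Working it through.** **Inputs from the article.** Two-sided alpha 0.05, 80% power, SD 3.7 days, detectable difference 1.3 days, 130 patients per period (all from Setting and Study Design).

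**Reproducing the plan's own figures.**
- Patients per period: 960 × 0.15 × 0.90 = 129.6, or 130.
- Needed for 1.3 days: 2 × (3.7 × (1.960 + 0.842) / 1.3)² gives 128 per period.
- Detectable difference at 130: (1.960 + 0.842) × 3.7 × √(2/130) = 1.29 days.
- Power for 1.3 days at 130: 80.9%.

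The sample size is therefore sound for its stated purpose.

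**Assumption for mortality.** Baseline hospital mortality is not given. The Introduction gives only a composite: 86% died or were discharged in severely compromised health. I therefore use a range of 30% to 70%.

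**Formulas, with n = 130 per period.**
- Half-width of the 95% interval when the rates are equal: 1.96 × √(2p(1−p)/n). At p = 0.5: 1.96 × √(0.5/130) = 0.122.
- Power for a rise d from p to q = p + d, with p̄ = (p + q)/2: Φ{[d − 1.96 × √(2p̄(1−p̄)/n)] / √([p(1−p) + q(1−q)]/n)}. At p = 0.5 and d = 0.10: Φ{(0.10 − 1.96 × 0.0617)/0.0614} = Φ(−0.34) = 0.37.
- Rise with 80% power: the smallest d, on a grid of 0.05 points, at which that formula reaches 0.80.

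| Assumed baseline | 95% CI half-width (points) | Power, +5 points | Power, +10 points | Rise with 80% power (points) |
|---|---|---|---|---|
| 30% | 11.1 | 14% | 39% | 16.85 |
| 40% | 11.9 | 13% | 37% | 17.30 |
| 50% | 12.2 | 12% | 37% | 17.05 |
| 60% | 11.9 | 13% | 39% | 16.15 |
| 70% | 11.1 | 14% | 46% | 14.55 |

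**An illustration.** Take 65 deaths of 130 before (50.0%) and 80 of 130 after (61.5%). The difference is 0.1154 and the pooled standard error is √(2 × 0.5577 × 0.4423/130) = 0.0616, so z = 1.87 and the test is not significant. The 95% interval, with unpooled standard error 0.0612, runs from −0.5 to +23.5 points.

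**What a margin would ask for.** The article gives no margin, so 5, 10 and 15 points are assumptions. For non-inferiority with one-sided alpha 0.025, 80% power and equal true rates, n = 2p(1−p)(1.960 + 0.842)²/margin². Power at n = 130 is Φ(margin/√(2p(1−p)/130) − 1.96).

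| Assumed margin | n per period for 80% power | Power at 130 per period |
|---|---|---|
| 5 points | 1319–1570 | 12–14% |
| 10 points | 330–393 | 36–42% |
| 15 points | 147–175 | 68–75% |

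The ranges cover baselines of 30% to 70%.

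**The case against.** **Mortality is secondary.** Aim 2 as worded concerns duration and intensity of treatment, and death is one category of a secondary outcome. Low power for a secondary outcome is not in itself an error. That stands, and the sample size is not faulted. But the sponsor wrote unchanged mortality into the objective and the hypothesis, so a test that cannot support it is a mismatch.

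**No text says that p > 0.05 means unchanged.** That is correct. Expected Results records an expectation, not a decision rule, and a reader should not infer that the plan commits to the misreading. An article may also leave margins and reporting rules to a fuller document. The point here is narrower: the article states both the claim and the test, and the two do not fit.

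**The chi-square test is not the only analysis that could touch mortality.** A reader might infer that it is. The planned regression on study outcomes could include death, with adjustment for severity and hospital. It is described as examining covariate effects and has no margin or criterion, so it does not close the gap.

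**The plan is not blind to hospice shifts or to deaths within the length-of-stay result.** Discharge to hospice is a recorded category, and other categorical outcomes are compared between periods. Outcomes are also stratified by ICU survivors and nonsurvivors. These stand as partial answers. The disposition comparison shows a shift into hospice only indirectly, and the stratification conditions on something that happens after the intervention begins.

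**Shorter stays among patients who die are a declared goal.** The plan treats ICU days in those patients as nonbeneficial. Earlier ICU death is thus not by itself evidence of failure under the plan's own terms, and this point does not claim that it is.

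**Conclusion.** The claim and the named test do not match. At 130 patients per period, a non-significant chi-square result would leave a rise of 10 points or more in hospital mortality compatible with the data. A true 10-point rise would be missed in 54% to 63% of studies.

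These figures rest on an assumed baseline of 30% to 70%, independent patients and normal approximations. The conclusion is the same across that range.

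A reader might go further and infer that the primary analysis is invalid or that the sample size is wrong. The documents do not support either: the length-of-stay calculation reproduces, and the defect is confined to what may be concluded about mortality.

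**What to change.** 1. In the Analysis Plan, report the difference in hospital mortality between periods with its 95% confidence interval, unadjusted and adjusted through the regression already planned. State that non-significance will not be read as no change.
2. Choose one of two routes. Either conclude that there is no material increase only if the upper confidence limit lies below a margin fixed and justified before analysis, and otherwise call the effect undetermined. Or reword the Abstract objective, the hypothesis and Expected Results so that mortality is a descriptive safety outcome.
3. Report the same analysis for death or discharge to hospice, which is already collected.
4. Optionally, show the cumulative incidence of ICU death and of live ICU discharge as competing events beside the rank-sum test.

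The cost is analysis and wording only, with no new data. The price is a weaker claim: even with a 10-point margin, power at 130 per period is 36–42% when mortality truly does not change, so the mortality conclusion will probably be undetermined.

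### The before-after test of nonbeneficial treatment is restricted to in-hospital deaths, a group the intervention can reshape, so it cannot carry an effect claim

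*Protocol article*

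**What the plan says.** The hypothesis in the protocol article (Objectives) is that the intervention "will decrease the duration and intensity of nonbeneficial ICU care without changing hospital mortality". The Analysis Plan first compares primary and secondary outcomes before and after the intervention in all patients. It then adds two analyses that depend on survival:

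- Outcomes "will also be analyzed and will be stratified by ICU survivors and nonsurvivors".
- ICU days, life-support days, invasive procedures and CPR attempts "among patients who did not survive hospitalization will be considered nonbeneficial treatment and will be compared before and after the intervention".

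The second is the only working definition the article gives of the nonbeneficial care named in the hypothesis. Expected Results adds a prediction of the same kind: reductions in ICU days, life-support days and procedures are expected "to be greater among patients who died during hospitalization than among survivors".

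Two other sections bear on who ends up in the nonsurvivor group. Under Time-Limited Trial Protocol, "if patients and surrogate decision makers wish for a palliative approach, the patient will be transitioned to comfort-focused care". Under Outcomes and Measurements, disposition is recorded as "outcomes of hospitalization (eg, death, discharge to hospice, skilled nursing facility, or home", so hospice discharge is a category apart from death. On mortality the article says "We expect mortality rates to remain unchanged before and after the intervention", and "ICU and hospital mortality rates will be compared using χ^2^ tests".

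**The concern.** In-hospital death and ICU death both happen after the intervention has begun, and the intervention works on the decisions that lead to them. Restricting a before-after comparison to the patients who died therefore compares two groups whose make-up the intervention may itself have changed.

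Two flows are easy to picture. A patient with a long ICU stay who would have died in hospital is discharged to hospice instead and leaves the nonsurvivor group. A patient with a short stay moves early to comfort-focused care and dies in hospital, and so enters it. Either flow lowers average ICU days among deaths although no one's ICU stay has changed. The opposite flows raise the average and could conceal a real reduction.

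At stake is the result closest in wording to the hypothesis. A drop in ICU days among deaths would naturally be reported as less nonbeneficial care, and the comparison cannot support that reading by itself. The predicted larger reduction in those who died than in survivors has the same weakness, since both strata can be reshaped.

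**Working it through.** **1. The plan's own figure.** Inputs from Setting and Study Design: 960 screened per period, 15% eligible, 10% of those excluded, SD 3.7 days, two-sided alpha 0.05, 80% power.

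- Patients per period: 960 × 0.15 × 0.90 = 129.6, or 130.
- Detectable difference: (1.960 + 0.842) × 3.7 × √(2/130) = 1.29 days, against 1.3 stated.

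The figure reproduces. It belongs to the all-patient comparison.

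**2. The same formula in deaths only.** The article gives no hospital mortality for the study population. The 86% in the Introduction combines death with discharge in a severely compromised state. Assume 50%, so 65 deaths per period: 2.802 × 3.7 × √(2/65) = 1.82 days.

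**3. Shift among deaths when no ICU stay changes.** Let a fraction *f* of would-be in-hospital deaths go to hospice, each with a chance proportional to ICU stay. The mean stay of those who move is mean + SD²/mean, so the mean among the remaining deaths shifts by

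−[*f*/(1 − *f*)] × SD²/mean = −[*f*/(1 − *f*)] × 13.69/6.5 = −[*f*/(1 − *f*)] × 2.106.

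| *f* | Shift by formula | Shift by simulation (gamma stay) |
|---|---|---|
| 10% | −0.23 | −0.23 |
| 20% | −0.53 | −0.53 |
| 30% | −0.90 | −0.89 |

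The last row differs slightly because in the simulation the chance of moving is capped at 1.

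**4. Direction depends on who moves.** With *f* = 20%, 50% mortality and a Wilcoxon test in deaths only:

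- Longer stays likelier to move: about −0.5 days, false rejection about 10%.
- Movement unrelated to stay: about 0 days, false rejection about 5%.
- Shorter stays likelier to move: about +0.4 days, which works against the study's hypothesis.

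**5. Does the mortality comparison protect?** Only weakly, for two reasons.

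- *Power.* At 130 per period, 80% power needs a rise of about 15 to 17 percentage points (baselines of 30% to 70%). In the 20% case above, hospital mortality falls from 50% to 40%, and power to detect that is about 37%.
- *Stable mortality is not enough.* Suppose above-median-stay deaths become live discharges and an equal number of below-median-stay survivors become in-hospital deaths, so that mortality is exactly constant. With 10/20/30% exchanged and 40% to 60% mortality assumed, mean ICU days among deaths shift by about −0.57/−1.13/−1.69. The deaths-only test then rejects in 14–19%/42–58%/76–89% of replicates, with no ICU stay altered. Selection by stay is deliberately strong here; the case shows that unchanged mortality does not exclude an artefact.

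**The case against.** The main test is sound. The primary outcome is ICU length of stay in everyone, the sample size rests on that comparison alone, and the secondary outcomes are also compared without restriction to deaths. The survival-based analyses come in addition, and nothing in the article calls them the main result. This stands, and it limits the point to those analyses and to the prediction in Expected Results.

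The magnitude rests on assumed inputs. The article gives no mortality rate, no hospice rate and no relation between ICU stay and hospice discharge. This also stands: the figures show that an artefact can arise, not that one will.

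Mortality is compared and hospice discharge is recorded, so a large shift from death to hospice would be seen. This stands only in part, because the mortality test has little power for moderate shifts and an exchange of patients can leave the rate unchanged. The planned regression on covariates such as severity and hospital may reduce the bias, but cannot be relied on to remove selection on an event that follows the intervention.

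Two stronger readings should be set aside. A reader might infer that hospice patients are counted as having received beneficial care. The Analysis Plan only leaves them out of the nonbeneficial group and says nothing about the value of their care. A reader might also see a contradiction between ICU survival and hospital survival, but these are two separate analyses, each labelled.

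**Conclusion.** The point holds for the comparison among hospital nonsurvivors, the ICU survivor and nonsurvivor strata, and the prediction of larger reductions in those who died. In each, patients are grouped by an event that the intervention can affect, so the groups before and after are not assured to be comparable. Calling them flatly non-comparable would go beyond the documents, which do not show that the groups differ.

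Size and direction are unknown. Under the stated assumptions (50% mortality, gamma stay with mean 6.5 and SD 3.7, 20% of would-be deaths moved to hospice, no ICU stay changed), the shift runs from about −0.5 days through 0 to about +0.4, according to who moves. If exactly the longest-stay 20% of would-be deaths moved, the shift would be about −1.4 days, and a reader might infer that the bias exceeds the effect the trial is sized for. Nothing in the article supports that extreme, and the 1.3-day figure belongs to 130 patients per period; for about 65 deaths per period the corresponding figure is 1.8. The all-patient comparison of ICU length of stay does not condition on death and is not affected.

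**What to change.** Amend the Analysis Plan and Expected Results as follows.

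1. Base the claim of reduced duration and intensity of ICU care on the all-patient comparisons of ICU days, life-support days, procedures and CPR attempts that are already planned.
2. Label the hospital-nonsurvivor results and the ICU survivor and nonsurvivor strata descriptive, and draw no effect claim from them, including the predicted larger reduction in those who died.
3. Report the rate of death or hospice discharge in each period, and add a sensitivity analysis that groups hospice discharge with in-hospital death.

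A score that counts ICU days for patients who die or go to hospice and 0 for everyone else should not become the effect test, because it still depends on disposition after the intervention. For example, with mean stay 6.5 and death or hospice rising from an assumed 50% to 60%, the mean score goes from 0.50 × 6.5 = 3.25 to 0.60 × 6.5 = 3.90, a rise of 0.65 days with no ICU day changed.

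The cost is a change of analysis wording; the variables are already among those to be collected. The downside is that the contrast among deaths no longer supports an effect claim.
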